## Abstract

**Background:**

Chronic fatigue and inactivity are prevalent problems among individuals with multiple sclerosis (MS) and may independently or interactively have detrimental effects on quality of life and ability to participate in life roles. However, no studies to date have systematically evaluated the benefits of an intervention for both managing fatigue and promoting physical activity in individuals with MS. This study involves a randomized controlled trial to examine the effectiveness of a telehealth intervention that supports individuals with MS in managing fatigue and increasing physical activity levels.

**Methods/Design:**

A randomly-allocated, three-parallel group, time-series design with a social support program serving as the control group will be used to accomplish the purpose of the study. Our goal is to recruit 189 ambulatory individuals with MS who will be randomized into one of three telehealth interventions: (1) a contact-control social support intervention, (2) a physical activity-only intervention, and (3) a physical activity plus fatigue management intervention. All interventions will last 12 weeks and will be delivered entirely over the phone. Our hypothesis is that, in comparison to the contact-control condition, both the physical activity-only intervention and the physical activity plus fatigue management intervention will yield significant increases in physical activity levels as well as improve fatigue and health and function, with the physical activity plus fatigue management intervention yielding significantly larger improvements. To test this hypothesis, outcome measures will be administered at Weeks 1, 12, and 24. Primary outcomes will be the Fatigue Impact Scale, the Godin Leisure-Time Exercise Questionnaire (GLTEQ), and Actigraph accelerometers. Secondary outcomes will include the SF-12 Survey, Mental Health Inventory, Multiple Sclerosis Impact Scale, the Community Participation Indicator, and psychosocial constructs (e.g., self-efficacy).

**Discussion:**

The proposed study is novel, in that it represents a multi-disciplinary effort to merge two promising lines of research on MS: fatigue management and physical activity promotion. Collectively, the proposed study will be the largest randomized controlled trial to examine the effects of a lifestyle physical activity intervention in people with MS.

**Trial registration:**

NCT01572714

## Background

Multiple sclerosis (MS) is an immune-mediated neurological disease that results in a variety of consequences, most notably fatigue and physical inactivity. In fact, 75-90% of people with MS report having fatigue, and 60% describe it as their most disabling symptom
[1-5]. Beyond fatigue, persons with MS are highly inactive compared with matched controls
[6], and this inactivity may increase the risk of developing secondary conditions (e.g., obesity, heart disease, and diabetes) that can accelerate MS-related functional decline
[7]. We further note that fatigue and physical inactivity may create a cyclical pattern of functional decline over time
[8].

One approach for managing fatigue and physical inactivity involves the development of behavioral interventions that focus on teaching self-management tasks and skills
[9]. For example, a randomized controlled trial (RCT) indicated that a fatigue self-management teleconference program was significantly more effective than a delayed-treatment control group for reducing fatigue impact and improving certain dimensions of health-related quality of life in persons with MS
[10]. The changes were maintained for six months after the intervention. Another RCT demonstrated that a behavioral intervention delivered via the Internet was effective in promoting and sustaining physical activity behavior change in ambulatory adults with MS
[11], and this effect was seemingly mediated by self-regulatory strategies of self-monitoring and goal-setting
[12].

To date, interventions for managing fatigue and physical inactivity have typically been addressed as separate lines of research, even though these two common consequences of MS are likely interrelated
[6,13,14]. The reciprocal relationship between fatigue and inactivity may accelerate a cycle of functional decline
[15]. MS fatigue can decrease motivation to engage in physical activity
[16,17]. Inactivity is associated with de-conditioning, mobility problems, depression, and further fatigue
[18-21], which makes it even more difficult to engage in physical activity
[22]. No study to date has systematically explored the combined benefits of teaching fatigue management strategies and promoting physical activity. We also note that the population with MS may have limited access to health professionals who can adequately address problems related to fatigue and inactivity, particularly for those who reside in rural communities
[23,24]. Therefore, using a telehealth approach to address the reciprocal relationship between MS fatigue and inactivity could increase the intervention’s accessibility and dissemination.

The objective of this proposed study is to conduct a RCT to examine the effectiveness of a telehealth intervention that supports individuals in managing fatigue and increasing physical activity levels. The proposed study is novel in that it represents a multi-disciplinary effort to merge two promising lines of research on MS: fatigue management and physical activity promotion. The proposed fatigue management plus physical activity intervention (FM+) will consist of incorporating a teleconference fatigue management intervention informed by the work of Packer et al.
[25], Finlayson et al.
[10], and Mathiowetz et al.
[26] with a novel, yet simple approach to promote lifestyle physical activity, i.e., encouraging goal-setting and self-monitoring with a pedometer. Our goal is to recruit 189 ambulatory individuals with MS who will be randomized into one of three telehealth interventions: (1) a contact-control social support intervention, (2) a physical activity-only intervention, and (3) a FM + intervention. Below we outline the aims, outcome measures, and associated hypotheses of the study.

### Specific aim 1

The first aim is to compare the effects of the three interventions on fatigue impact and physical activity levels. Outcomes will be the Fatigue Impact Scale (FIS)
[27], the Godin Leisure-Time Exercise Questionnaire (GLTEQ)
[28], and Actigraph accelerometers. Our hypothesis is that, in comparison to the contact-control condition, both interventions will yield significant improvements in FIS scores and physical activity levels, with the FM+ yielding significantly larger improvements.

### Specific aim 2

The second aim is to compare the effects of the three interventions on health-related quality of life, mental health, and participation in life roles. Outcomes will be the SF-12, Mental Health Inventory (MHI), Multiple Sclerosis Impact Scale (MSIS)
[29,30], and the Community Participation Indicator (CPI)
[31,32]. Our hypothesis is that, in comparison to the contact-control condition, both interventions will yield a significant increase in SF-12, MHI, MSIS, and CPI scores, with the FM + yielding a significantly larger increase.

### Specific aim 3

The third aim is to identify potential mediators of the interventions. Psychosocial constructs measures related to fatigue and physical activity (e.g., self-efficacy, goal-setting, and outcome expectations) will be administered to help identify the underlying mechanisms of the interventions’ possible effectiveness. Our hypothesis is that scores on these measures will significantly improve, and that improvements will explain the interventions’ effect on fatigue and physical activity.

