#### Contact-control social support intervention

The contact control group will consist of the same number of contacts as the FM+, i.e., six weekly one-hour teleconference calls with four biweekly one-to-one phone calls. Thus, this condition will allow us to determine whether it is the actual content being taught in the goal-setting physical activity intervention and FM+ intervention that is beneficial, rather than simply the contacts with the OT or social support provided by other group members. The teleconference calls and the one-to-one calls will involve a discussion of topics commonly addressed in support groups. Topics will include information on MS, disease modifying medications, preventive screening, community organizations, nutrition and supplements, cognitive problems, and recognizing symptoms of depression and chronic stress. For the teleconference sessions, participants will be given the opportunity to share problems and provide peer support and solutions for others. For the one-to-one calls, participants will be asked about topics of interest, and the graduate student will gather educational materials and send them to the participant. This information will be the basis for the discussion in the calls. When issues related to fatigue and physical activity are raised, participants will be directed to publically available educational pamphlets. This type of social support group has been used successfully in other clinical trials as a control condition to evaluate the efficacy of fatigue management programs in persons with MS
[40].

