##### Secondary dependent variables

Health-related quality of life, mental health, and participation in life roles will be measured with the SF-12, Mental Health Inventory, and Community Participation Indicator (CPI), respectively. The SF-12 and Mental Health Inventory are valid and reliable measures, and are commonly used in the population with MS
[43]. The CPI is a new measure developed by Heinemann and colleagues. The measure was developed with input from multiple stakeholders, and has been validated through Rasch analysis in a sample of 1,163 individuals with a variety of disabling conditions
[31,32]. In a subsequent online survey study, the measure had good test-retest reliability over a 2.5 month period in people with MS (t = 0.12, p = 0.91; r = 0.84, p < 0.01). For each item, respondents rate the frequency of engagement (either in days, hours, or times per week, depending on the type of activity), whether it was important (yes/no), and whether they were doing it not enough, enough, or too much. Examples of the 20 items included are: work for money, provide care for a loved one, volunteer, and participate in learning activities.

Six questionnaires will be implemented to identify underlying mechanisms of the interventions’ possible effectiveness for increasing physical activity levels and reducing fatigue impact. Psychosocial construct measures for physical activity will be the Self-Efficacy for Exercise Scale
[44], Exercise Goal-Setting Scale
[12,45], and Multidimensional Outcome Expectations Scale
[46]. All three questionnaires are validated and have been used in previous MS research on physical activity
[45,47]. Psychosocial construct measures for fatigue management will be the validated Self-Efficacy for Performing Energy Conservation Strategies
[48] along with two additional measures on goal-setting and outcome expectations, which will be developed and validated during the study.

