##### Data management and analysis

A secure online application, Research Electronic Data Capture
[49], will be used to manage recruitment efforts and facilitate data collection. The first step in the analysis process will be to compute summary statistics, calculate outcome scores, and conduct quality control assessments. The second step in the analysis will be to test whether the randomization process resulted in equivalent groups at baseline. If differences are found at baseline, these variables will be used as covariates during the hypothesis testing phase. The third step in the analysis process will be addressing normality assumptions, and the potential for missing data, before hypothesis testing begins. If the normality assumption is violated, then an appropriate data transformation will be used. Missing data will be treated conservatively. If appropriate, maximum likelihood, multiple imputation, or last observation carried forward will be used to estimate the missing values. After addressing issues of attrition and missing data, the fourth step will be to conduct intent-to-treat analysis to test the hypotheses. Linear mixed-effects models will be used as the primary analysis tool for testing hypotheses, which include condition, time, and interactions as the fixed covariates, and a random intercept that models the correlation among outcomes collected from the same subject. The mixed models will allow us to determine whether there are significant differences between the three conditions and whether there are significant differences across time. All tests will be two-sided, and p = 0.05 will serve as the criterion for significance. As is typically the case for mixed-effects analyses, the results will not be controlled for multiple comparisons. The generalized estimating equation approaches will be used if the normality distributional assumption is violated for the random effects in the mixed models. To test for mediation, we will use a linear regression model. This analysis will first involve regressing changes in fatigue impact or physical activity on the intervention conditions, and then regressing changes in fatigue or physical activity on the intervention conditions plus changes in the potential mediator. Mediation will be based on the interventions’ association with physical activity or fatigue impact being reduced in magnitude and non-significant after controlling for the mediator variable.

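### The first clause of Aim 3 predicts better mediator scores without the control comparison used in Aims 1 and 2, and the mediation rule never asks whether the intervention moved the mediator (minor)

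*Protocol article*

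**What the plan says.** All references are to the protocol article.

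- **Specific aim 1** is comparative: "in comparison to the contact-control condition, both interventions will yield significant improvements in FIS scores and physical activity levels". Specific aim 2 uses the same comparator.
- **Specific aim 3** is one sentence in two parts. The first is "Our hypothesis is that scores on these measures will significantly improve", with no comparator. The second is "and that improvements will explain the interventions’ effect on fatigue and physical activity".
- **Secondary dependent variables** describes the scales: "Six questionnaires will be implemented to identify underlying mechanisms of the interventions’ possible effectiveness". Three concern physical activity and three concern fatigue management.
- **Data management and analysis** tests hypotheses with linear mixed models, "which include condition, time, and interactions as the fixed covariates". These are to show differences between the three conditions and also "whether there are significant differences across time".
- **Mediation**, in the same section, has two regressions. The first is "regressing changes in fatigue impact or physical activity on the intervention conditions". The second adds change in the candidate mediator. Mediation is declared if the condition effect becomes smaller and non-significant. Tests are two-sided at 0.05, without adjustment for multiple comparisons.

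**The concern.** A variable can carry an intervention's effect only if the intervention changes it relative to control. Neither the first clause of Aim 3 nor either mediation regression asks for that.

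A rise shared by all arms is conceivable here. The same scales are completed three times. The physical activity-only section lists role modelling through members' stories as one way to raise self-efficacy, and in the control arm "participants will be given the opportunity to share problems and provide peer support and solutions for others". The control exists to separate taught content from contact and support, yet the first clause does not call on it.

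Two things are at stake. A statement that the psychosocial scores improved could rest on a time effect alone. And a scale could be named as a mechanism because an adjusted p-value drifted past 0.05.

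**Working it through.** The plan gives no figure of its own for Aim 3, so there is none to reproduce. It supplies 63 per arm, 20% attrition and a between-visit correlation of 0.5 (Sample size), and two-sided 0.05.

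**1. How easily a common rise meets the first clause**

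- Completers: 63 × 0.8 = 50.4 per arm; 3 × 50.4 = 151.2 pooled.
- SD of change: sqrt(2 × (1 − 0.5)) = 1 SD.
- Standard error of mean change: 1/sqrt(50.4) = 0.141 per arm; 1/sqrt(151.2) = 0.081 pooled.
- Power from the noncentral t, with no intervention effect on the scale. The size of the rise is assumed.

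| Common rise (SD) | Change within one arm significant | Time effect over all arms significant |
|---|---|---|
| 0.2 | 29% | 69% |
| 0.3 | 55% | 96% |
| 0.4 | 80% | 99.8% |

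The contrast with control stays at 5% throughout. The within-arm column is for scale only, since the article plans no within-arm test.

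**2. Whether a common rise meets the whole hypothesis**

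The plan's rule was simulated with 4,000 trials per scenario, three arms of 50 and the FM+ versus control coefficient. It was read as requiring a significant condition effect in the first regression, then a smaller and non-significant one in the second. Assumed: common rise 0.3 or 0.5 SD, mediator-outcome correlation 0.3 or 0.5, effect on the outcome 0 or 0.6 SD, no effect on the mediator.

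- Pooled improvement significant: 95-100%.
- Condition effect on the mediator significant: about 5%, the nominal level.
- Improvement and mediation rule both met: about 1-2.6%.
- With a 0.6 SD outcome effect, the median ratio of adjusted to unadjusted condition coefficient was 0.98-0.99, so there was almost no attenuation.

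**3. Where chance attenuation comes from**

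For FM+ versus control the standard error is sqrt(1/50 + 1/50) = 0.2. An effect of 0.6 SD gives t near 0.6/0.2 = 3.0, which a small shift rarely carries below the cut-off. An effect of 0.3 SD gives t near 0.3/0.2 = 1.5, so trials that reach significance do so narrowly and a small imbalance in the mediator can undo it. Allowing for such effects raises the per-scale figure to about 1-4%.

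**4. Six scales**

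Assumed: each scale rises 0.3 SD in every arm, correlation between scales about 0.5, scale-outcome correlation 0.3-0.5, FM+ effect on the outcome between 0 and 0.6 SD. At least one unaffected scale met both parts in about 3-13% of trials, for one outcome and one contrast. Requiring also that mediator change differ from control reduced this to about 1-5%.

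**5. Cost to true mediators**

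With 50 per arm, a true 0.6 SD difference in mediator change is detected against control with power of about 0.85. The added requirement could then remove at most 15 percentage points of correct declarations. The loss is larger for weaker effects on the mediator.

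**The case against.** A reader might infer that a rise common to all arms would confirm Aim 3, or that the trial plans an uncontrolled before-after analysis. The document supports neither.

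- The Aim 3 sentence has a second required part tied to the between-arm effect, and step 2 shows that a common rise rarely meets both.
- The mixed model contains condition and its interaction with time, and no exception is made for Aim 3. The statement about differences across time sits beside one about differences between conditions.
- The abstract gives a control-referenced hypothesis and lists the psychosocial constructs among the secondary outcomes measured to test it. Methods/Design says the controlled design serves the study's aims. It cannot be said that the control would go unused.
- Eligibility selects on inactivity and fatigue, not on self-efficacy, goal-setting or outcome expectations, so regression to the mean on those scales is not established. The size of any common rise is assumed.
- The attenuation rule covers the condition-to-mediator path indirectly, since a mediator balanced across arms hardly moves the coefficient.

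All of this stands and keeps the point small. Two things remain: the first clause as printed lacks the comparator its sister aims carry, and the printed rule admits chance attenuation because it never tests the mediator against control.

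**Conclusion.** The point holds as a minor one. A common rise would satisfy the first clause of Aim 3, but not the two-part hypothesis. Under the printed rule, an unaffected scale is labelled a mediator in about 1-4% of trials, and at least one of six in about 3-13%.

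These figures rest on assumed correlations, rises and effects and on 50 completers per arm, and cover one outcome and one contrast. Three primary measures and unadjusted testing would push the trial-wide figure up. Pairing each outcome with only its own three scales would pull it down, and the article does not say which is meant. The per-scale rate alone is not alarming. The case for acting is that the remedy needs nothing not already planned.

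**What to change.** 1. In the first clause of Specific aim 3, state that improvement is relative to the contact-control condition, as in Aims 1 and 2.
2. Test that clause by the condition-by-time contrast already in the mixed model, not by the time effect.
3. In the mediation paragraph, add a regression of mediator change on condition, and call a scale a mediator only if this shows a difference from control.

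The cost is a phrase in Aim 3 and a sentence in the analysis section. No new data are needed. The mediation criterion becomes slightly stricter, with somewhat less power to declare true mediators. Scale-specific hypotheses comparing FM+ with physical activity-only are optional and not needed for this repair.

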## Methods/Design

A randomly-allocated, three-parallel group, time-series design with a social support program serving as the control group will be used to accomplish the aims of the study. Outcome measures will be administered at Weeks 1, 12, and 24. All interventions will involve a 12-week intervention period (three or six teleconference sessions weekly, and four one-to-one phone calls every other week) followed by a 12-week non-contact period to determine whether the effects persist. The design will enable us to compare the overall immediate and sustained outcomes of the three interventions. The protocol is approved by the Cleveland Clinic’s Institutional Review Board (ref: 11-844) in accordance with the Declaration of Helsinki. The study is funded by the National Multiple Sclerosis Society.

### Sample size

In order to achieve an adequate power of 0.80 to test hypotheses, we will seek to recruit a total of 189 individuals for this study and, more specifically, 63 in each condition. The total number of individuals to be recruited is based on calculations of sample size and power for a balanced repeated-measure mixed effect model with three time points (Weeks 1, 12, and 24) using a formula provided by Hedeker et al.
[33]. We assumed equal variance and correlation (rho = 0.5) between measures across time points, and an effect size of 0.6 at Weeks 12 and 24. These calculations account for 20% attrition over time.

### Recruitment and eligibility

Individuals for this study will be recruited in several different ways in the State of Ohio. We have restricted recruitment to Ohio to avoid complications with state licensure laws. Fliers for the study will be distributed through MS support groups and National MS Society and MS Association of America events. We will recruit through physician referral and electronic health record review, and an MS patient registry maintained by the North American Research Consortium on MS (NARCOMS), which has approximately 400 registered individuals in Ohio who are ambulatory. Regardless of the recruitment method, individuals who are interested in participating in the study will be asked to contact the study office. Potential participants will undergo a telephone screening procedure to determine eligibility, and then a confirmation of eligibility through contacting their physician.

Inclusion criteria are: (1) physician-confirmed diagnosis of MS and physician-consent to initiate a physical activity program, (2) age between 18 and 65 years, (3) ability to walk at least 25 feet with a cane, (4) ability to carry on telephone conservations in English, (5) a Patient Determined Disease Step score between 1 (mild disability) and 5 (unilateral support required)
[34], (6) a current sedentary lifestyle (i.e., purposeful exercises ≤ 2 days per week for 30 minutes)
[35], and (7) experiences moderate to severe fatigue (a score of ≥ 4 on the Fatigue Severity Scale)
[36]. Exclusion criteria are: (1) pregnancy, (2) cardiopulmonary diseases, (3) uncontrolled diabetes (hospitalized within the last six months), (4) greater than three falls in the past six months, and (5) severe cognitive deficits (weighted score of less than 12 on the short version of the Blessed Orientation Memory Concentration test)
[37].

